## Abstract

**Background:**

Bipolar Disorder (BD) is a common and severe form of mental illness characterised by repeated relapses of mania or depression. Pharmacotherapy is the main treatment currently offered, but this has only limited effectiveness. A recent Cochrane review has reported that adding psycho-social interventions that train people to recognise and manage the early warning signs of their relapses is effective in increasing time to recurrence, improving social functioning and in reducing hospitalisations. However, the review also highlights the difficulties in offering these interventions within standard mental health services due to the need for highly trained therapists and extensive input of time. There is a need to explore the potential for developing Early Warning Sign (EWS) interventions in ways that will enhance dissemination.

**Methods and design:**

This article describes a cluster-randomised trial to assess the feasibility of training care coordinators (CCs) in community mental health teams (CMHTs) to offer Enhanced Relapse Prevention (ERP) to people with Bipolar Disorder. CMHTs in the North West of England are randomised to either receive training in ERP and to offer this to their clients, or to continue to offer treatment as usual (TAU). The main aims of the study are (1) to determine the acceptability of the intervention, training and outcome measures (2) to assess the feasibility of the design as measured by rates of recruitment, retention, attendance and direct feedback from participants (3) to estimate the design effect of clustering for key outcome variables (4) to estimate the effect size of the impact of the intervention on outcome. In this paper we provide a rationale for the study design, briefly outline the ERP intervention, and describe in detail the study protocol.

**Discussion:**

This information will be useful to researchers attempting to carry out similar feasibility assessments of clinical effectiveness trials and in particular cluster randomised controlled trials.

## Background

Bipolar Disorder (BD) is a common and severe form of mental illness characterised by repeated relapses of mania or depression. Recurrence rates are high at around 50% at one year and 70% at four years [1,2]. Pharmacotherapy is the main treatment currently offered, but this has only limited effectiveness [3]. Surveys of patient organisations in the United States (US) and United Kingdom (UK) reveal a strong wish by patients for both self-help and psychological treatments in addition to pharmacotherapy [4,5]. One form of intervention is to teach patients with BD to recognise and manage early warning signs (EWS) of mania and depressive episodes. A recent systematic review of this approach found that 11 RCTs involving 1324 patients show the efficacy of interventions that include this approach [6]. Overall, EWS interventions, in addition to treatment as usual, increased time to recurrence and reduced the percentage of people hospitalised. Despite having no clear impact on depressive or manic inter-episode symptoms, there was some evidence that EWS interventions had a positive impact on levels of functioning.

Most of these studies reviewed involved interventions consisting of extensive hours of therapy with highly trained therapists, clearly restricting their generalisability to current NHS services. The review highlights the need for further research to explore cost-effective ways in which these interventions can be offered within the NHS. Bauer et al (2006) showed that positive outcomes for reducing relapse into mania could be achieved within Veterans Affairs hospitals in the US using a chronic care model in which people are transferred to a specialist team providing group psychoeducation, improved pharmacotherapy guidelines, and coordinated care to enhance communication within services [7,8]. Although demonstrated to be cost-neutral, this intervention required setting up new specialist bipolar disorder teams and the benefits for service users were only apparent by the third year of being in such a service [7]. Although designed to address issues of external validity, generalising from these settings to the UK NHS and probably other health settings is problematic because there is no political will to provide brand new services specifically and only for service users with BD [9]. However, there is political will to adapt existing services to meet the needs of service users with BD more specifically.

The least resource intensive intervention in a UK study was that by Perry et al (1999) in which a median of 9 sessions were offered by a minimally trained research psychologist in addition to treatment as usual (TAU) and demonstrated a fourfold increase in time to next manic episode in people receiving Relapse Prevention (RP) compared to those receiving treatment as usual only, and a 30% reduction in number of manic episodes over 18 months[10]. The intervention did not detect an impact on depressive episodes. This is likely to be due to greater difficulty in identifying EWS of depression, lack of clear coping strategies for these signs, and delay in response to anti-depressant medication.

In this study we have devised an enhanced form of a RP approach, which is enhanced by an increased focus on the identification of EWS for depression, more detailed development of coping strategies available for both depression and mania, and the involvement of a relative/friend to support the intervention where appropriate. The key elements of the ERP intervention are those explicitly recommended by the NICE Guidelines for Bipolar Disorder [9], and include psychoeducation, a detailed analysis of previous episodes, identification of trigger situations and early warning signs, enhancing coping strategies for mood changes, an action plan for responding to early warning signs, and an agreement with clinical services about how they will respond to different stages of relapse. These elements are done separately for mania, depression and mixed episodes. The intervention is used alongside other interventions such as pharmacotherapy.

In addition to the enhancements to the RP approach, this study differs significantly from those described previously (including Perry et al (1999)) in that the ERP intervention will be offered to people with Bipolar Disorder by Care Coordinators (CCs) currently working in Community Mental Health Teams (CMHTs) in the National Health Service (NHS). A CMHT is a multidisciplinary team of health professionals (community mental health nurses, occupational therapists, psychiatric social workers, clinical psychologists and psychiatrists) working out of a team base in the geographical locality the CMHT serves. The CMHT sees service users at the base, other clinic bases or in the home of the service user. All service users with serious mental illness whose needs require more than the support of one professional group would be looked after by a CMHT with one of the health professionals in the team acting as a CC taking the lead role for coordinating the care of the patient but not delivering all aspects of the patient's care [11]. All service users in the CMHT will have as a minimum a CC and a psychiatrist but there may also be other members of the CMHT or other health or social service professionals who would provide specific services to the service user with BD. Hence, this study focuses on issues related to the clinical effectiveness of relapse prevention in a real world setting that uses existing CCs and is able to examine the impact and the barriers that arise in this situation. We are aiming to address the important issue of transferring evidence-based interventions from psychological research settings into NHS practice. Interventions that have been shown to be clinically efficacious under ideal conditions may not be effective in clinical practice [12]. The approach is consistent with the Department of Health remit for CMHTs to offer psychological interventions aimed at preventing relapse in people with severe mental illnesses ("such as schizophrenia and bipolar disorder") and to work with both patients and carers [11].

The approach relies on a quick and reliable response from the CMHTs to changes in patients' symptoms and therefore the intervention must be offered by the team as a whole, rather than by individual CCs. Once trained, these teams would be unable to offer treatment as usual. Thus in order to assess the effectiveness of the intervention, a cluster randomised controlled trial (RCT) is needed in which the CMHT is the unit of randomisation. Effectiveness can be assessed at two levels; firstly, the effectiveness of the training on the ability of the CCs to carry out the key elements of the ERP interventions; secondly the effectiveness of the CC delivered ERP intervention on reducing relapse rates in people with Bipolar Disorder.

A large-scale evaluation of the effectiveness of the ERP intervention is required. However, this is likely to be a very expensive study due to the costs of training staff and the recruitment, assessment and retention of large numbers of staff, service users and relatives. Therefore it is important that the study is theoretically well designed, methodologically feasible, adequately powered to identify any impact the intervention has on outcome, and well executed. To enable this to happen, essential information is required that will be obtained from this study. This includes: an understanding of what current TAU is for people with Bipolar Disorder who are offered a service by CMHTs; acceptability of the ERP intervention, training and supervision packages; effectiveness of training and supervision on Care Coordinator competency and confidence to offer ERP; recruitment and retention rates for CMHTs, individual Care Coordinators, service users with BD and relatives; acceptability, validity and reliability of assessment measures including those modified for the study; identification of major barriers to carrying out the project within the NHS; an estimate of the effect size of the intervention; an estimate of the design effect of clustering. Detailed evaluation of process variables will allow the mechanism of action to be understood so that important inferences can be drawn in terms of the wider implementation of the intervention. This trial is an example of a Phase II exploratory trial in the Medical Research Council (MRC) framework for development and evaluation of RCTs for complex interventions to improve health [13]. Reporting the details of the study design also contributes to a widely recognised need for increased sharing of information from pilot studies of cluster trials to improve methodological developments in this area [14].

The aim of the trial is to assess the feasibility of a large cluster randomised trial to evaluate the effectiveness of training CCs in ERP for people with bipolar disorder.

The aim of this paper is to outline the ERP intervention, provide a rationale for the study design, and describe in detail the study protocol. Future papers will give a detailed description of the intervention and the process of training and will report on the feasibility and effectiveness of the training and the impact of this on relapse rates for people with Bipolar Disorder.

## Methods

### Structure of the trial

The trial is conducted by multidisciplinary researchers based across 3 academic institutions, and CMHT staff working in the NHS. The trial is funded by the Medical Research Council and Merseycare NHS Trust, sponsored by the University of Liverpool, and is supported by an independent Trial Steering Committee consisting of service users, researchers, clinicians and statisticians. Ethical approval through Central Office for Research Ethics Committees (COREC) and Research & Development (R&D) approval at each Trust has been given.

### Design

ERP is a stratified cluster randomised controlled trial with extensive evaluation of the process as well as the outcome of the trial. CMHTs are randomly allocated to receive training and supervision in ERP or to continue to offer Treatment as Usual (TAU). The number of teams in each Trust is identified prior to randomisation. The variable for stratification is NHS Trust. This is to take into account different systems and approaches for working with Bipolar Disorder between Trusts and also any changes in guidelines for working with BD that may appear during the period of study. Teams are allocated numbers, which are then randomised electronically. Service users with BD from teams in both arms are assessed by researchers blind to allocation on a range of outcome measures for up to 48 weeks following the onset of treatment. All incidences of unblinding are recorded.

A cluster design is considered necessary because all members of a CMHT need to be able to understand and implement an individual relapse prevention plan for all service users. Although each service user has a named CC, other members of the team are closely involved in their care through out-of-hours cover, crisis management, co-working etc. Therefore any training aimed at modifying practice should be offered to teams rather than individuals. Data from service users with Bipolar Disorder who are within the same cluster i.e. seen by the same team, are not independent. Other variables, such as team set-up, previous team training, management style, etc. are likely to influence the outcome of the intervention. Failing to account for this clustering effect is may result in under-powered studies [15].

### Sample

#### Sample size

A power calculation is not applicable for this study. The aim of the feasibility study is to collect information that will allow us to estimate the effect size for ERP compared to TAU and to estimate the impact of using a cluster randomised design (intra-class correlation coefficient). This information will allow a meaningful sample size calculation to be made for a large-scale definitive effectiveness trial (Phase III within the MRC complex interventions framework).

#### Inclusion/Exclusion criteria

All CMHTs across 4 North West NHS Trusts are invited to take part in the trial. Specialist teams such as Assertive Outreach Teams (AOTs), Crisis Teams, Home Treatment Teams, and Early Intervention Teams are excluded.

Teams are included in the randomisation if a minimum of 4 CCs gives informed consent to take part in the study. This includes agreeing to attend the training and supervision and to offer the intervention to a minimum of 3 service users each if the team is allocated to ERP. CMHTs working from the same building with extensive clinical cover are entered as one team. This reduces the possibility of any contamination between teams allocated to different arms of the trial.

Staff with a range of backgrounds are invited to take part in the training (nurses, occupational therapists, and social workers), but must be identified Care Coordinators for service users. Support workers are excluded from the study but are invited to sit in on the training where resources allowed.

Service users are invited to take part if they had a lifetime diagnosis of Bipolar I or II, have experienced two or more relapse ever and at least one in the last year or two in the last three years, and are currently not in a major depressive, hypomanic, manic or mixed episode in the last four weeks. Service users are excluded if there is a clear organic cause of their disorder, they have a rapid cycling disorder, they have significant cognitive impairment, they have alcohol/drug misuse as a primary diagnosis, they do not have a working understanding of English language, or they are unable or unwilling to give informed consent.

#### Recruitment and consent

All CMHTs in the participating NHS Trusts are given a verbal presentation about the study and written information sheets. A minimum of 4 CCs from each team are asked to give written consent to invite service users into the study, to attend the training and supervision if allocated to the ERP arm of the trial, and to provide quantitative and qualitative feedback on the training and supervision.

Service users with a clinical diagnosis of Bipolar Disorder are initially informed about the study by their CC. We obtain lists of service users who would seem to meet the inclusion/exclusion criteria for the study according to the CMHT prior to the randomisation of teams to prevent any bias in the numbers of service users who are recruited to the two arms of the study. Recruitment occurring post-randomisation of the CMHTs is noted and rates of recruitment monitored to identify any post-randomisation selection bias or impact on recruitment rates. Service users are asked to consent to their contact details being passed to the research team in order to receive more information about the study. Those who consent are sent a letter and a visit is arranged with a researcher who gives verbal and written information about the study. Service users are then asked to give written consent in two parts. The first part consents them to take part in the data collection for the study, and the second to take part in the clinical intervention, if they are allocated to the ERP arm of the trial. This ensures that participants who drop out of the intervention, can still take part in the research study if they wish [16].

Service users offered ERP are invited to involve a relative/friend in the intervention. Where this occurs, the relative/friend is asked by the CC to give written consent to take part in the study. Following the intervention, the relative/friend is invited to give qualitative feedback on their experiences. Figure 1 gives an outline of the design of the study.

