#### Impact of the intervention on outcome

An estimate of the effect size of the intervention will be made from a comparison of time from baseline to recurrence of an episode of major depression, hypomania, mania, or mixed, satisfying DSM-IV criteria [19] following at least 8 weeks below this level for that pole. The number and percentage of patients satisfying criteria for a DSM-IV episode, broken down by type (major depression; mania type; other), will be reported for each treatment group and overall. The number and percentage of patients for whom information is imputed will also be reported. The intervals (in days) from baseline to recurrence (of any type) will be summarised by Kaplan-Meier curves (plotted up to 48 weeks). Cox proportional hazard models with robust variance estimators will be used to provide estimates of the hazard ratios and 95% confidence intervals.

The main analyses will be conducted on all patients from all teams (assigned to treatment groups (ERP and TAU) as randomised), applying the principle of intention to treat (ITT), as far as is practically possible, given any missing data. Sensitivity analyses based on a "per protocol" (PP) analysis will be conducted to examine robustness of the main results to departure from intended trial treatment. The sample of patients for the PP analyses is defined as the sample for the ITT analyses minus those patients who could not have received sufficient trial treatment due to CCs not attending at least 4 training sessions, or service users receiving less than 4 sessions of ERP. Given that the study is a feasibility study used in part to estimate the sample size for a larger study, effect sizes with 95% confidence intervals will be given weight rather than reliance on levels of statistical significance alone.

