There are a number of important limitations to the study that need to be addressed in future work. Firstly, this study is designed to assess the impact of clustering at the level of CMHT and to account for this in the statistical analysis of outcome. However, in reality the study has 2 levels of clustering: the CMHT and the Care Coordinator. Each Care Coordinator is asked to offer the ERP intervention to a minimum of 3 service users. It could be argued that data from service users who receive the intervention from the same Care Coordinator is likely to be correlated more highly than that from different Care Coordinators within the same team. However, due to the fact that the number of people within each cluster at the CC level would be likely to be very small i.e. 3, and the total sample would be insufficient to explore multiple level clustering, this will not be accounted for in the analysis.

Secondly, we have argued that a cluster design is required because ERP is essentially a team approach. Service users may need to be able to contact the CMHT at very short notice in response to increased recognition of important changes in their early signs of relapse. An effective and reliable response from the team is essential. For this reason, whichever CMHT staff member is currently on duty should be able to work with the ERP plan. In reality, we have recruited teams with a minimum of 4 CCs consenting to take part. This is for purely pragmatic reasons. In setting up the study, services felt unable to commit the time and resources for all staff to attend. Although the documentation regarding early signs monitoring and action plans is available in the service users notes, future work needs to address the best ways to disseminate information within and between mental health teams. It is possible that this limitation will reduce the effectiveness of the intervention.

Thirdly, due to the time constraints on the study, we are unable to recruit all service users prior to randomisation at each NHS Trust site. CCs make referrals throughout the study and generally offer ERP sequentially to one person at a time. Teams in TAU also make referrals throughout as more people who are eligible are identified. We are assessing and will report on whether or not this has led to a recruitment bias.

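### Recruitment rates, the only stated check for selection bias after team randomisation, cannot show whether the arms recruited people with different prognosis

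*Protocol article*

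**What the plan says.** Teams, not patients, are randomised (Protocol article, Design). Under Recruitment and consent, the first approach to patients is made by staff of those teams: "Service users with a clinical diagnosis of Bipolar Disorder are initially informed about the study by their CC". Lists of apparently eligible service users are obtained "prior to the randomisation of teams to prevent any bias in the numbers of service users who are recruited to the two arms". For people who enter later, the same section says: "Recruitment occurring post-randomisation of the CMHTs is noted and rates of recruitment monitored to identify any post-randomisation selection bias or impact on recruitment rates".

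The third limitation in the Discussion concedes that "we are unable to recruit all service users prior to randomisation at each NHS Trust site", and adds that "CCs make referrals throughout the study and generally offer ERP sequentially to one person at a time". It says that TAU teams also refer throughout, and that the authors will report whether a recruitment bias arose. It does not say how this will be judged.

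Under Impact of the intervention on outcome, "The main analyses will be conducted on all patients from all teams", as randomised. The one sensitivity analysis named there is per protocol, defined by training and therapy sessions attended. Under Potential confounds, number of previous episodes, social support and medication use are among the factors to be controlled for.

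**The concern.** Once a team is randomised, its care coordinators know the arm: ERP coordinators attend the training and TAU coordinators do not. For later referrals, the person who brings a patient into the trial is therefore not blind to what that patient will receive. The incentives also differ, because ERP coordinators have agreed to deliver the intervention to at least three service users each and TAU coordinators have no such task. Blind outcome assessment does not help, since the selection happens before assessment.

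The protocol links the right problem to the wrong measure. A difference in recruitment rates is one possible sign of selection, but the bias in the hazard ratio comes from a difference in who is recruited. If the two arms recruit at the same rate, a rates check will look reassuring whatever the prognostic mix.

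Two outputs of the study are at stake. The estimated effect is meant to inform the sample size of the definitive trial. The study is also meant to show whether this design is feasible, and recruitment by unblinded staff is one of the features to be judged.

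**Working it through.** The article states no sample size, power, event count or share of late referrals, so there is no figure of the plan's own to reproduce. The calculation below asks only whether equal recruitment rates can coexist with a biased hazard ratio.

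**Inputs from the Protocol article**
- Recurrence of about 50% at one year (Background).
- Follow-up to 48 weeks (Design; Table 1).

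**Assumptions, not in the document**
- Constant hazard, no true effect (HR = 1), and equal numbers recruited per arm, so the recruitment-rate ratio is 1.00.
- A share *s* of the ERP arm are late referrals with hazard *h* times that of everyone else. TAU has no such selection.
- No covariate adjustment.

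**Steps**
1. Weekly hazard: λ = ln 2 / 52 = 0.01333.
2. TAU at 48 weeks: S = exp(−48 × 0.01333) = 0.527, so recurrence is 47.3%.
3. ERP at 48 weeks: S_ERP = (1 − s)·S + s·S^h.
4. Apparent HR (ratio of cumulative hazards) = ln S_ERP / ln S, with ln S = −0.640.

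For s = 0.5 and h = 0.8: S^0.8 = 0.599, S_ERP = 0.563, ln S_ERP = −0.574, apparent HR = 0.574/0.640 = 0.90.

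For s = 0.5 and h = 0.7: S^0.7 = 0.639, S_ERP = 0.583, ln S_ERP = −0.539, apparent HR = 0.539/0.640 = 0.84. (Simulating the same mixture gives 0.85; the difference is one of method.)

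| Late share of ERP arm | h = 0.85 | h = 0.80 | h = 0.70 | h = 0.50 |
|---|---|---|---|---|
| 25% | 0.96 | 0.95 | 0.92 | 0.86 |
| 50% | 0.92 | 0.90 | 0.84 | 0.73 |
| 75% | 0.89 | 0.85 | 0.77 | 0.61 |

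The recruitment-rate ratio is 1.00 in every cell.

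**Other directions.** If TAU teams select in the same way and to the same extent, numerator and denominator are equal and the apparent HR is 1.00. If ERP coordinators instead refer people more prone to relapse, say h = 1.25 with s = 0.5, then S^1.25 = 0.449, S_ERP = 0.488, ln S_ERP = −0.717, and the apparent HR is 0.717/0.640 = 1.12. Rates cannot tell these cases apart either.

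**Consequence for the definitive trial, as an illustration.** Required events scale as 1/(ln HR)². If the true HR were 0.80 and selection multiplied it by 0.90, to 0.72, the planned events would be (ln 0.80 / ln 0.72)² = (0.223/0.329)² = 0.46 of the number needed.

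**The case against.** The strongest reply is that the article does more than watch rates. It takes lists before randomisation, notes which recruitment came afterwards, promises to report on recruitment bias, and will control for confounds. Baseline depression and mania scores, dates of the last episode, three-year episode history and medication are all collected. The authors disclose the limitation and attribute it to time constraints. A fuller analysis plan, not shown, may describe the comparison of baseline characteristics.

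Most of this stands, and it rules out three stronger readings that a reader might draw.
- *That rates are all the trial will look at, so selective referral would go undetected.* The Discussion's promise is not limited to rates, and the data for a better check are being gathered.
- *That all service users are referred with the allocation known.* The article says only that not everyone can be recruited beforehand, and the share is not given.
- *That the effect of ERP will be exaggerated.* TAU teams also refer throughout, the article does not say how ERP coordinators decide whom to see next, and the eligibility rules on recent relapse and current episodes limit the scope for picking stable patients. The bias could be small, absent or in the other direction.

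The reply does not remove the specific fault. The only method the article names for identifying selection bias cannot identify a difference in prognosis. That is a statement in the text, not a detail left to another document. The adjustment handles measured factors only, and a coordinator's private judgement of motivation or stability is not among those named. The per-protocol analysis addresses departure from treatment, and by dropping service users with fewer than four ERP sessions it adds no protection against selection.

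**Conclusion.** The point holds in a limited form. Some service users enter after their care coordinator knows the allocation. The stated means of identifying the resulting bias measures numbers when the threat lies in prognosis. The promised report has no stated method, and the main analysis does not separate people identified before randomisation from those identified after it.

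The direction and size of any bias are unknown. With half of the ERP arm as late referrals at 0.7 to 0.8 times the hazard and no such selection in TAU, a null effect would show as an HR of about 0.84 to 0.90 before adjustment. That figure shows what a rates check could miss; it does not forecast the trial's result. It depends on an assumed share, an assumed relative hazard and selection in one arm only, and adjustment for previous episodes and medication might remove part of it.

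The change is worth making because the estimate is meant to feed the design of the definitive trial and the data needed are already being collected.

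**What to change.** 1. Record for each participant whether they were named on the pre-randomisation list, alongside the timing of recruitment that is already noted.
2. State that the promised assessment of recruitment bias will compare baseline prognosis (previous episodes, time since last episode, Hamilton depression score, Bech-Rafaelsen mania score) by arm and by recruitment timing. It should also compare the proportion of listed service users who consent in each arm. Recruitment rates can stay as a supplement.
3. Report the recurrence hazard ratio restricted to listed participants as a sensitivity analysis beside the all-patient analysis.

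An arm-by-listed interaction test is not recommended. The trial has no power calculation, and its sample is described as too small to model a second level of clustering. If the interaction is shown at all, it should be descriptive.

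The cost is one data flag, one baseline table and one extra model. The restricted analysis will have fewer patients and a wider confidence interval. It is not fully protected, because care coordinators also make the first approach to listed service users and consent may differ by arm. The consent proportions in step 2 are there to show that.
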